## Abstract

**Background:**

Babies born after midtrimester preterm prelabour rupture of membranes (PPROM) are at risk to develop neonatal pulmonary hypoplasia. Perinatal mortality and morbidity after this complication is high. Oligohydramnios in the midtrimester following PPROM is considered to cause a delay in lung development. Repeated transabdominal amnioinfusion with the objective to alleviate oligohydramnios might prevent this complication and might improve neonatal outcome.

**Methods/Design:**

Women with PPROM and persisting oligohydramnios between 16 and 24 weeks gestational age will be asked to participate in a multi-centre randomised controlled trial. Intervention: random allocation to (repeated) abdominal amnioinfusion (intervention) or expectant management (control). The primary outcome is perinatal mortality. Secondary outcomes are lethal pulmonary hypoplasia, non-lethal pulmonary hypoplasia, survival till discharge from NICU, neonatal mortality, chronic lung disease (CLD), number of days ventilatory support, necrotizing enterocolitis (NEC), periventricular leucomalacia (PVL) more than grade I, severe intraventricular hemorrhage (IVH) more than grade II, proven neonatal sepsis, gestational age at delivery, time to delivery, indication for delivery, successful amnioinfusion, placental abruption, cord prolapse, chorioamnionitis, fetal trauma due to puncture. The study will be evaluated according to intention to treat. To show a decrease in perinatal mortality from 70% to 35%, we need to randomise two groups of 28 women (two sided test, β-error 0.2 and α-error 0.05).

**Discussion:**

This study will answer the question if (repeated) abdominal amnioinfusion after midtrimester PPROM with associated oligohydramnios improves perinatal survival and prevents pulmonary hypoplasia and other neonatal morbidities. Moreover, it will assess the risks associated with this procedure.

**Trial registration:**

NTR3492 Dutch Trial Register (http://www.trialregister.nl).

## Background

Preterm prelabour rupture of membranes (PPROM) before or near the limit of viability is associated with high perinatal morbidity and mortality. Respiratory complications are frequent after periviable PPROM, as well as sepsis, intraventricular haemorrhage, retinopathy and necrotising enterocolitis (NEC). Among respiratory complications pulmonary hypoplasia is an important cause of death. Other respiratory complications consist of pneumonia, Infant respiratory distress syndrome (IRDS) and bronchopulmonary dysplasia (BPD).

PPROM before 26 weeks can delay lung development and can cause pulmonary hypoplasia [1]. Pulmonary hypoplasia is a term to describe an altered pulmonary development characterised by a reduction in the number of pulmonary alveoli or in bronchial branching. In fetal lung development a critical interval, the canalicular phase, exists between 16 and 28 weeks gestation. Gestational age at rupture of membranes has been shown to be inversely related to the risk of pulmonary hypoplasia.

Pulmonary hypoplasia results in severe respiratory failure leading to early neonatal death, respiratory insufficiency with pulmonary haemorrhage, bronchopulmonary dysplasia, or sub-acute lung disease, or sometimes in mild transient respiratory disease [2]. Perinatal mortality approximates 70% in most series (55-100%) [3].

In a review of 11 studies on midtrimester PPROM, the reported incidence of pulmonary hypoplasia secondary to midtrimester PPROM ranged widely from 1% to 48% [4]. A review of 6 studies on PPROM before 24 weeks reported an incidence of pulmonary hypoplasia of 19% (n = 120) [5]. These percentages do not represent the true natural history, given the limitations of these reviews, summarising only retrospective cohorts from tertiary care centres. The wide range in prevalence is partly explained by the absence of uniform pathological and clinical definitions. Histological findings form the basis of the diagnosis pulmonary hypoplasia, however complete autopsy data were often not available [2]. An international recognized definition of pulmonary hypoplasia is lacking, and it rather is a diagnosis by exclusion [6]. Congenital pneumonia, infant respiratory distress syndrome (IRDS) and pulmonary hypoplasia sometimes occur simultaneously, and have overlapping symptoms [1]. Moreover, there were methodological problems in the reviews, such as differences in follow-up and lack of blinded assessment of the endpoints.

Pregnancies complicated by midtrimester PPROM are associated with high immediate and long-term costs. These are caused by extended maternal hospital admissions, increased incidence of premature delivery, and frequent neonatal complications hereafter requiring NICU-admission.

Amnioinfusion might improve fetal outcome by preventing pulmonary hypoplasia, by preventing neurological complications, increasing time to delivery interval, and improving fetal biophysical profile through prevention of umbilical cord compression. It also might prevent fetal deformity [7]. Porat et al. [8] reviewed serial transabdominal amnioinfusion and meta-analysed observational as wel as randomised studies. The only two included randomised studies however were on women with PPROM between 24 and 34 weeks whereas the critical interval for development of pulmonary hypoplasia, the canalicular phase, exists between 16 and 28 weeks gestation. One quasi-randomised study included women with PPROM before 24 weeks. There were two observational studies on PPROM before 24 weeks. Recently, Roberts et al. [9] published the only randomized trial on PPROM between 16 and 24 weeks. They found no difference in the primary outcome (perinatal mortality 19/28 vs. 19/28; RR 1.0; 95% CI0.70-1.43), maternal or neonatal morbidity. The observed difference in long term outcome (4/28 morbidity free survival at 2 years in the treatment group vs 0/28 in the group with expectant management) justifies further study.

Adverse events after antepartum transabdominal amnioinfusion have been reported. It is not clear which adverse effects are to be attributed to the procedure rather than to the condition of PPROM and oligohydramnios, since conservatively managed PPROM carries high risks inherent to the condition itself [7]. Waters and Mercer recently reviewed perinatal mortality after conservatively managed PPROM <26 weeks [5]. Meta-analysis of 6 studies (n = 275) shows a perinatal mortality of 54%, (if restricted to <24 weeks this incidence is 57%). These data are biased by the fact that patients not amenable to continued expectant management were often excluded (i.e. stillbirths, pregnancy terminations), and therefore survival is likely to be overestimated.

## Methods/Design

### Aims

The primary aim of this study is to evaluate the effectiveness of amnioinfusion compared to expectant management for relieving oligohydramnios in women with midtrimester PPROM occurring before 24 weeks gestational age in reducing perinatal mortality and neonatal morbidities.

### Participants/eligibility criteria

All women with a singleton pregnancy who are first diagnosed between 16 and 24 weeks gestational age with oligohydramnios secondary to PPROM, at least 72 hours after PPROM was diagnosed, but no longer than 21 days after the diagnosis of oligohydramnios, are eligible for the trial. Women with oligohydramnios secondary to iatrogenic PPROM are also eligible.

We will exclude women with signs of uterine contractions, (8 uterine contractions per hour) intrauterine infection (temperature > 38°C plus fetal tachycardia or uterine tenderness or foul/purulent amniotic fluid), a pregnancy complication (hypertension, HELLP syndrome, preeclampsia or other) in which there is a need for termination of pregnancy, placental or major structural fetal anomalies, signs of cervical incompetence (visible cervical dilatation or a cervical length of <25 mm), and women whose child has signs of fetal distress (abnormal biophysical profile).

### Procedures, recruitment, randomisation and collection of data

The research nurse and/or the staff of participating hospitals will identify eligible women. Prior to randomisation, in all patients amniotic fluid loss will be objectified by sterile speculum examination for visible fluid loss from the cervical os, by a nitrazine- and/or ferning test. Speculum examination will be performed to exclude signs of cervical incompetence (visible dilatation). Hereafter patients will undergo an ultrasound examination to determine the single deepest pocket (SDP) of amniotic fluid and to exclude placental and or fetal structural anomalies. At this time ultrasound measurements used in the prediction of pulmonary hypoplasia - TC/AC (thoracic circumference/abdominal circumference), TC/FL (thoracic circumference/femur length), Doppler measurement of pulmonary artery proximal branch peak systolic velocity, 3D lung volume measurement -, will be performed by specialized personnel.

If oligohydramnios is present (SDP < 2 cm) patients will be counselled for the study. Randomisation, will take place immediately after informed consent has been obtained, at least 72 hours after diagnosis of PPROM. See also Figure 1.

**Figure 1 F1:**
[figure not shown]
Flowchart PPROMEXIL-III trial.

Randomisation will be performed, using an internet-based procedure, with the use of a permuted-block design, after informed consent and baseline data have been entered in a web-based database system.

Treatment allocation will obviously have to be unblinded for patients and clinicians and sonographers, and the personnel performing the ultrasound investigations, however, allocation will remain blinded for paediatricians, pathologists and/or radiologists who are assessing outcomes.

All data are collected, coded and processed with adequate precautions to ensure patient confidentiality. The investigators will publish the results of the study in a peer reviewed medical journal as soon as appropriate.

### Interventions

The intervention being evaluated is trans-abdominal amnioinfusion. After sterile preparation of the abdomen, a pocket of fluid is identified by ultrasound guidance after which a needle is advanced into this pocket. After insuring proper placement by withdrawing a small amount of fluid, the desired volume of fluid (Ringers lactate), defined by the number of weeks of gestational age times 10 millilitres, is infused manually. This procedure is repeated on a weekly basis if oligohydramnios re-occurs or persists.

If, after initial amnioinfusion, uterine contractions and signs of infection have been excluded, discharge is optional. Fluid retention will be assessed by measurement of SDP 48–72 hours after first amnioinfusion. Five to seven days after initial amnioinfusion, SDP is reassessed, as well as infection parameters (white cell count and CRP). Measurement of TC/AC, TC/FL, Doppler measurement, 3D lung volume measurement, will be performed by specialised personnel. If persisting or re-occurring oligohydramnios is diagnosed, amnioinfusion will be repeated. The same procedure will be repeated on a weekly basis until 28 weeks’ gestation.

Patients randomised to expectant management will undergo the same clinical and ultrasound examination bi-weekly (once a week measurement of SDP, TC/AC, TC/FL, Doppler, 3D lung volume, infection parameters, and on the second weekly visit assessment of fetal well-being and measurement of SDP). These patients can, if signs of premature labour or infection have been excluded, at the discretion of the local physician, be discharged as well (Figure 1). All discharged patients will be instructed to take their temperature twice daily and contact the hospital in case of fever (temperature > 37.8°C, rectally measured) or suspected infection. Patients with midtrimester PPROM are usually hospitalised after 24 weeks in a tertiary centre.

### Use of co-intervention

Corticosteroids are given according to local protocol, usage will be recorded in the case report form. All patients will receive treatment with antibiotics (Erythromycin orally 250 mg 4 times per day for ten days).

Patients may stop participating in the study at any time for any reason if they wish to do so without any consequences. The investigator can decide to withdraw a subject from the study for urgent medical reasons.

### Study parameters/endpoints

We will compare two groups:

1) Amnioinfusion for midtrimester PPROM with oligohydramnios, and

2) Expectant management for midtrimester PPROM with oligohydramnios.

The primary outcome measure will be perinatal mortality, defined as intrauterine death, intrapartum death or neonatal death in the first 28 days of life.

Secondary outcomes are:

• Gestational age at delivery.

• Time from membrane rupture to delivery.

• Indication for delivery.

• Successful amnioinfusion (defined as retention of infused fluid as defined by a single deepest pocket of amniotic fluid of more than 2 cm for at least 48 hours).

• Placental abruption.

• Cord prolapse.

• Chorioamnionitis, (defined as fever before or during labour as a temperature greater than 37.5°C on two occasion more than one hour apart or a temperature > 38.0°C with either uterine tenderness (or contractions), leucocytosis, maternal or fetal tachycardia, or a foul-smelling vaginal discharge in absence of any other cause of hyperpyrexia).

• Fetal trauma due to puncture.

• Maternal length of stay in hospital.

Occurrence of secondary outcomes placental abruption, cord prolapse, chorioamnionitis and fetal trauma will be related to the number of amnioinfusions that have been performed.

Neonatal endpoints:

• Lethal pulmonary hypoplasia diagnosed according to radiological, clinical and pathological criteria. Pathological criteria are based on radial alveolar counts and lung/body weight ratios according to Askenazi and Perlman [11], when radial alveolar counts cannot be obtained, criteria by Wigglesworth et al. will be used [12]. Clinical criteria used to diagnose lethal pulmonary hypoplasia are: immediate onset of severe respiratory insufficiency after birth, small lung capacity and requirement of high ventilatory pressures in the absence of obstruction or atelectasis. Radiological criteria according to Leonidas will be used [13].

• Non-lethal pulmonary hypoplasia diagnosed using same clinical and radiological criteria in surviving neonates.

• Survival till discharge from NICU.

• Neonatal mortality, defined as neonatal death in the first 28 days of life.

• Chronic lung disease (CLD), CLD defined as oxygen dependency at 28 days of life [14].

• Number of days on ventilatory support.

• Length of stay in hospital.

• Necrotising enterocolitis (NEC) more than stage I and defined according to the criteria of Bell et al. [15].

• Periventricular leukomalacia (PVL) more than grade I and defined according to the classification described by De Vries et al. [16].

• Severe intraventricular hemorrhage (IVH) more than grade II and defined according to the criteria of Papile et al. [17].

• Proven neonatal sepsis defined as (1) Positive blood culture taken at birth or (2) within 72 hours two or more symptoms of infection (apnea, temperature instability, lethargy, feeding, intolerance, respiratory distress, hemodynamic instability) plus one of three items: (a) positive blood culture (culture proven sepsis); (b) CRP > 20 (suspicion sepsis); (c) positive surface cultures of a known virulent pathogen (suspicion sepsis).

The neonatal endpoints will be defined by two neonatologists. The status of these endpoints will be evaluated at six months corrected age. Additional application for long-term follow-up of children (2 and 5 years) and mothers will be performed.

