### Sample size calculation

A sample size calculation was based on an expected rate of perinatal mortality of 70% with expectant management, to be reduced to 35% with amnioinfusion. Using a two-sided test, with a β-error of 0.20 and an α-error of 0.05 a sample size of 56 women (28 in each arm) is needed.

An interim analysis is planned after the follow up data of the first 28 women that have been included. The analysis will be performed using the O’Brien-Flemming alpha spending function meaning a nominal P value of less than 0.005 will be considered to indicate statistical significance [16]. If there is a significant difference in the primary outcome the trial will be stopped.

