### Statistical analysis

The analysis of the randomised clinical trial will be performed on an intention-to-treat principle. The differences between the amnioinfusion and expectant management will be assessed by calculating the ratio of the outcome rates in the two groups. Hence, the measure of association is a relative risk (RR) with a 95% confidence interval (CI), calculated using a log-binomial model. Time to delivery will be evaluated by Cox proportional hazard analysis, Kaplan-Meier estimates and tested with a log rank test.

In case of equivalence between outcomes, the analysis will be repeated on an “as-treated” basis. Subsequently, primary and secondary outcomes will be described in a subgroup of women with successful amnioinfusion (retention of infused fluid first 48 hours). All analyses will be adjusted for the fact that an interim analysis will be performed using the O’Brien-Flemming alpha spending function [18]. Consequently, a nominal P value of less than 0.049 will be considered to indicate statistical significance.

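### Time to delivery is counted from membrane rupture, before randomisation, so its survival curves include guaranteed event-free time, and variable entry delays can dilute the arm comparison

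*Protocol article*

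**What the plan says.** Among the secondary outcomes, Study parameters/endpoints lists "Time from membrane rupture to delivery". No other time-to-delivery outcome is defined. Under Statistical analysis: "Time to delivery will be evaluated by Cox proportional hazard analysis, Kaplan-Meier estimates and tested with a log rank test". That sentence gives no origin and does not mention delayed entry.

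Entry comes later than rupture. Under Procedures, recruitment, randomisation and collection of data: "Randomisation, will take place immediately after informed consent has been obtained, at least 72 hours after diagnosis of PPROM". Under Participants/eligibility criteria the window is "at least 72 hours after PPROM was diagnosed, but no longer than 21 days after the diagnosis of oligohydramnios". Its lower limit runs from the diagnosis of PPROM and its upper limit from a different date, the diagnosis of oligohydramnios. The delay from rupture to randomisation therefore has no explicit cap of its own.

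**The concern.** A woman who delivers before randomisation cannot be in the trial. Every randomised woman is therefore undelivered, by design, from rupture to randomisation. A standard analysis from rupture nevertheless puts her in the risk set during that time, which neither arm's management can affect.

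Two things follow:

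- **Curves and medians.** The Kaplan-Meier estimates include event-free time that was guaranteed by the entry rule. They do not estimate latency from rupture in all women with PPROM, because early deliveries are excluded. They do not estimate latency after assignment either, because the clock starts too early.
- **Comparison of arms.** If the delay differs between women, it adds variation unrelated to treatment to each observed time. That can move the hazard ratio toward 1 and cost power.

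The outcome matters because the Background section names a longer interval to delivery as one way in which amnioinfusion might help. The trial has only 56 women.

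**Working it through.** **1. The plan's own figure.** The article gives no figure for time to delivery. Its sample size concerns perinatal mortality (Sample size calculation: 70% against 35%, two-sided α 0.05, β 0.20). The unpooled two-proportion formula reproduces it:

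n per arm = (1.960 + 0.842)² × (0.70×0.30 + 0.35×0.65) / 0.35² = 7.849 × 0.4375 / 0.1225 = 28.03, matching the stated 28. This point does not touch that figure.

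**2. A common delay.** Write the time from rupture as X = D + T, where D is the delay to randomisation and T the time from randomisation to delivery. If D is the same for all women, X is T shifted by a constant. The order of deliveries and the risk set at each delivery are unchanged, so the log-rank and Cox results are identical. Simulation with D = 3 days for all and a 20-day control median gave hazard ratio 0.495 and power 71.3% for both origins. The Kaplan-Meier curve still moves right by 3 days.

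**3. A variable delay: effect on the median.** The documents give no distribution for D or T, so these are assumptions. Let T be exponential with a 7-day median (rate λ = 0.693/7 = 0.0990 per day) and D uniform on 3 to b days. For t between 3 and b:

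P(X > t) = (b − t)/(b − 3) + [1 − exp(−λ(t − 3))] / [λ(b − 3)]

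- b = 24, t = 22: 0.095 + 0.408 = 0.503, so the median from rupture is about 22 days, against 7 from randomisation.
- b = 35, t = 28: 0.219 + 0.289 = 0.508, so the median is about 28 days, against 7.

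**4. A variable delay: effect on the comparison.** Simulation with 28 per arm, all followed to delivery, true hazard ratio 0.50 from randomisation, constant hazard, two-sided 0.05. As a benchmark, the usual approximation with 56 events gives z = √(56/4) × ln 2 − 1.96 = 0.63, a power of about 74%. The simulated power from randomisation is about 70-72%.

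| Control median | Power loss from using rupture, delays 3-24 or 3-35 days |
|---|---|
| 7 days | about 5-13 points |
| 14 days | about 2-6 points |
| 28 days | about 0-2 points |

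A separate set with other assumed values points the same way:

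| Control median, delay | Hazard ratio: randomisation → rupture | Power: randomisation → rupture |
|---|---|---|
| 10 days, 3-24 days | 0.488 → 0.503 | 71.4% → 68.9% |
| 10 days, 3-42 days | 0.493 → 0.536 | 72.1% → 61.2% |
| 40 days, 3-42 days | 0.498 → 0.499 | 69.6% → 69.5% |

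**5. Hazard shape.** With a falling hazard (Weibull shape 0.6) the loss is at most about 4 points. With a rising hazard (shape 1.5) and short latency it is larger. The most extreme setting tested (hazard rising with time since rupture, scale 10 days, delays 3-42 days) moved the hazard ratio from 0.51 to 0.69 and power from 67% to 27%.

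**6. Under no effect.** With a true hazard ratio of 1.0, rejection was about 5-6% for every origin.

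**7. Which remedy recovers the loss.** Counting from randomisation gave a hazard ratio of 0.49-0.51 in every setting. Rupture as origin with delayed entry at randomisation did as well when the hazard was constant or ran on time since rupture. It recovered only part of the loss when a rising hazard ran on time since randomisation (for example power 54.7%, against 70.6% from randomisation and 40.8% from rupture without delayed entry).

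**The case against.** The case for leaving the text alone has several parts.

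- **The link is inferred.** Statistical analysis speaks only of time to delivery. Applying the rupture origin to the Cox and log-rank analyses means reading two sections together. This stands as a caveat. The reading is reasonable all the same, because the article defines no other time-to-delivery outcome. Nor is this only detail left to an analysis plan, since the article itself fixes the origin.
- **The size rests on assumptions.** This stands. The losses of 5-13 points need a 7-day control median. The eligibility criteria exclude women with contractions, infection or a short or dilated cervix, which fits longer latencies at least as well, and there the loss is small.
- **A median from rupture is a different quantity, not an inflated one.** This largely stands. The gap of about 15 or 21 days in step 3 is mostly the change of origin. What remains is that the rupture-based median applies only to women still undelivered at randomisation.
- **The outcome is secondary**, and gestational age at delivery is listed separately as another view of prolongation. This stands and limits the weight of the point.

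Two stronger readings are tempting, and the documents support neither. A reader might infer that the 72-hour rule itself weakens the test; step 2 shows that a common shift changes nothing. A reader might also infer an immortal-time bias that favours one arm. The delay ends at randomisation, so it is balanced in expectation, and step 6 shows no inflation of type I error.

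**Conclusion.** The point holds in a limited form. Read as written, the plan analyses time to delivery from a date before randomisation and without delayed entry. The Kaplan-Meier curves and medians then mix guaranteed event-free time with latency after assignment, whatever the latency distribution.

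The cost to the arm comparison is conditional. It depends on how much the delay varies relative to latency after randomisation, and the documents give neither. It ranges from nothing (equal delays) or next to nothing (long latency) to roughly 13 power points under constant hazard at a 7-day control median, and more if the hazard rises. The error is toward no difference. The primary outcome and the sample size of 28 per arm are unaffected. This is worth correcting because the correction is so cheap, but it does not threaten the trial's main conclusion.

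**What to change.** In Study parameters/endpoints and Statistical analysis, define the outcome for the Cox, Kaplan-Meier and log-rank analyses as time from randomisation to delivery. Keep latency from rupture as a descriptive figure, with a note that it applies to women undelivered at randomisation, or analyse it with delayed entry (left truncation) at randomisation. Randomisation is the better origin for the main comparison because it held the hazard ratio in every setting tested.

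The cost is a change of wording and no extra patients. It needs the dates of randomisation and delivery, plus the date of rupture for the descriptive figure. The article does not list the dates collected, so this should be confirmed. The one small downside is a less direct comparison with cohorts that report latency from rupture, and the descriptive figure covers that.

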### Safety reporting

This study has been approved by the ethics committee (METC) of the Academic Medical Centre Amsterdam and by the boards of management of all participating hospitals.

In accordance with the National Medical Research Act (WMO, Section 10, Subsection 1), the investigator will inform the subjects and the reviewing accredited METC in case it appears that the disadvantages of participation may be significantly greater than was foreseen in the research proposal. All observed or volunteered adverse events, regardless of suspected causal relationship to the intervention, will be recorded.

An adverse event (AE) is defined as an event after which the intervention has to be stopped. Reasons for discontinuation are placental abruption, cord prolapse, chorioamnionitis, fetal loss, fetal trauma due to puncture, premature labour and delivery.

A serious adverse event (SAE) is defined as fetal or maternal death or illness necessitating IC or CCU treatment. All SAEs will be reported to the accredited METC that approved the protocol, according to the requirements of that METC. In addition to the expedited reporting of SAE’s, the principal investigator will submit, once a year throughout the clinical trial, a safety report to the accredited METC.

A Data Safety Monitoring Board (DSMB) will be established prior to start of the trial.

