## Discussion

There are signs that pregnancies complicated by oligohydramnios after midtrimester PPROM might benefit from amnioinfusion. However, currently there is insufficient evidence to recommend this procedure. The benefits might be increased neonatal survival and decreased pulmonary complications, especially pulmonary hypoplasia. Potential harms include placental abruption, premature labour and delivery, cord prolapse, chorioamnionitis, fetal loss, fetal trauma due to puncture. Of these, only the last mentioned is not a known potential complication of the underlying condition itself as well (midtrimester PPROM). Expectant management indeed carries these same risks. At present, there is no evidence on which a rational choice between expectant management or therapeutic amnioifusion can be based.

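### Relating complications to the total number of amnioinfusions can hide harm, because the same complications stop the infusions; the AE and SAE definitions also need repair

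*Protocol article*

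**What the plan says.** All references are to the Methods/Design part of the protocol article unless stated.

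- **Study parameters/endpoints**, after the list of maternal and obstetric secondary outcomes: "Occurrence of secondary outcomes placental abruption, cord prolapse, chorioamnionitis and fetal trauma will be related to the number of amnioinfusions that have been performed".
- **Safety reporting**: "Reasons for discontinuation are placental abruption, cord prolapse, chorioamnionitis, fetal loss, fetal trauma due to puncture, premature labour and delivery".
- **Interventions**: "If persisting or re-occurring oligohydramnios is diagnosed, amnioinfusion will be repeated", and "The same procedure will be repeated on a weekly basis until 28 weeks" of gestation. A further infusion thus needs a woman who is undelivered, has had no stopping event and has low fluid again.
- **Safety reporting**, on definitions: "An adverse event (AE) is defined as an event after which the intervention has to be stopped". Just before this stands "All observed or volunteered adverse events, regardless of suspected causal relationship to the intervention, will be recorded". Then: "A serious adverse event (SAE) is defined as fetal or maternal death or illness necessitating IC or CCU treatment".
- **Discussion**, on the listed harms other than puncture trauma: "Expectant management indeed carries these same risks".

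The abstract says that the trial will assess the risks of the procedure.

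**The concern.** The number of infusions a woman ends up with is not fixed in advance. A woman whose membranes become infected after the first infusion has a count of one because she had the complication. A woman who reaches a high count does so because she had none until then. The exposure in the planned relation is therefore cut short by the outcome, which is reverse causation. A reader who sees no rise in complications with the count could wrongly conclude that repeating the procedure adds no risk.

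The two definitions raise a related problem. An adverse event defined by stopping an intervention has no clear meaning for women who never receive it. The SAE definition names fetal and maternal death but not neonatal death, although neonatal death up to day 28 is part of the primary outcome.

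**Working it through.** The article gives no figure for this analysis and no weekly hazards. All hazards below are assumptions, chosen to show what the planned relation can and cannot reveal.

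**1. Overlap of outcomes and stopping reasons**

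| Event | Related to infusion count | Reason to stop infusing |
|---|---|---|
| Placental abruption | yes | yes |
| Cord prolapse | yes | yes |
| Chorioamnionitis | yes | yes |
| Fetal puncture trauma | yes | yes |
| Fetal loss, premature labour, delivery | no | yes |

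All four outcomes end the count.

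**2. Closed form**

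Let each infusion carry the same risk *h* of a stopping complication. Let *d* be the chance of delivery before the next infusion if there is no complication, and let *K* be the largest possible count. A woman with exactly *n* < *K* infusions stopped either through a complication (*h*) or through delivery, (1 − *h*)*d*. So

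P(complication | *n* infusions) = *h* / [*h* + *d*(1 − *h*)] for every *n* < *K*, and *h* at *n* = *K*.

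With *h* = 0.10, *d* = 0.10, *K* = 6: 0.10 / (0.10 + 0.09) = 53% for 1 to 5 infusions, and 10% at 6. The true cumulative risk, 1 − 0.9^*n*, is 10% at 1, 27% at 3 and 47% at 6. The planned relation is flat and then falls, while the real risk rises.

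**3. With a background risk**

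Assume 3% weekly background complications, 10% weekly delivery, entry spread evenly over weeks 17 to 23, an infusion every week through week 28, and events counted through week 36. Below the cap the formula in step 2 applies with 0.03 + *h* in place of *h*. For *h* = 0.10, for example: 0.13 / (0.13 + 0.10 × 0.87) = 60%.

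| Added risk per infusion | 1 infusion | 2-3 | 4 or more |
|---|---|---|---|
| 0 | 24% | 24% | 20% |
| 5 points | 47% | 47% | 36% |
| 10 points | 60% | 60% | 48% |
| 20 points | 75% | 75% | 66% |

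Reading across a row gives no sign of harm. The harm appears only between rows, that is, against women who are not infused. The risk in the week after each infusion is 0.03 + *h* (3%, 8%, 13%, 23%) at every infusion number, so a per-procedure analysis shows it directly.

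**4. The direction is not fixed**

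All three variants start from the 10% delivery, 3% background model; the first and third add 10 points per infusion.

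- Delivery at 30% a week: 33%, 33%, 31% (nearly flat).
- Harm that starts at 5 points and grows by 5 points with each infusion: 46%, 64%, 75% (rising).
- 40% of women retain fluid after the first infusion and need no more: 37%, 60%, 48% (correlation with the count +0.04).

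**5. The size depends on follow-up after 28 weeks**

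Assume no infusion effect, 5% weekly complications, 10% weekly delivery, entry over weeks 17 to 24 and infusions through week 27.

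| Events counted | 1-2 infusions | 3-5 | 6 or more |
|---|---|---|---|
| until 28 weeks only | 34% | 24% | 14% |
| through week 37 | 34% | 32% | 30% |

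The middle figure of the first row becomes 28% if entry ends at week 23. Most of the steep gradient comes from ignoring later events, and the article sets no 28-week limit on these outcomes.

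**6. Neonatal deaths and the SAE definition**

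In the Dutch cohort of 164 singletons cited in the Background, perinatal mortality was 71%, of which 38% was neonatal. So 0.71 × 0.38 = 27% of pregnancies, or 0.27 × 28 = 7.6, about 7 to 8 in an arm of 28 at that rate. The SAE definition covers these only where illness needing intensive care preceded the death. A death at birth without intensive care is not clearly covered.

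**The case against.** **No model is fixed.** The sentence says only that occurrence will be related to the count. A full protocol or SAP could do this by procedure or with a time-dependent covariate, and an article may leave such detail out. This stands in part: the method is open. But the article does fix the exposure as the number of infusions performed, and that choice is the problem. A later document would have to replace it, not just add detail.

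**More infusions must look safer.** A reader might infer that the relation is inverse by construction. Steps 4 and 5 do not support this. The pattern can be inverse, flat or rising, depending on the delivery rate, fluid retention, follow-up after 28 weeks and whether harm accumulates.

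**No safety comparison with controls is left.** A reader might infer this from the AE definition. The article does not support it. The complications are secondary outcomes of a two-group comparison analysed by intention to treat with relative risks, all adverse events are to be recorded whatever their cause, and the SAE definition is not tied to stopping. Only the literal AE label fails in controls.

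**Neonatal deaths are not lost.** This stands. They count in the primary outcome and as a named secondary outcome in both arms, and some will meet the intensive-care criterion. The gap concerns SAE reporting, not the trial's results.

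**Conclusion.** The point holds in limited form. The total number of infusions is partly determined by the complications it is meant to explain, so the stated relation cannot measure harm per infusion and can hide harm or suggest protection. That conclusion follows from the article's own stopping list and needs no assumed figures. Every gradient shown above rests on assumed hazards and is illustrative only.

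Separately, the AE definition and the sentence on recording all adverse events must be reconciled, and the SAE definition leaves a gap for neonatal death.

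The primary outcome and the randomised comparison of complications are not affected. The point should be corrected, but it does not threaten the main result.

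**What to change.** 1. Replace the analysis by total count with complications per procedure, counted in a fixed window after each infusion (for example 7 days), with confidence intervals that allow for repeated procedures in the same woman.
2. As optional support, enter cumulative infusions as a time-dependent covariate from randomisation. With about 28 infused women this will be imprecise, and it remains confounded because repeat infusion depends on persisting oligohydramnios.
3. State that the randomised between-arm comparison is the main safety evidence. Report fetal puncture trauma in the amnioinfusion arm only.
4. In Safety reporting, define AEs identically in both arms without reference to stopping, so that the definition agrees with the recording sentence. Keep the list of stopping reasons as a separate item; nothing here asks for a change to it.
5. Name neonatal death in the SAE definition.

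Cost: a little more analysis work, recording of infusion and event dates (the article does not say whether these are already collected), and a few more SAE reports.
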